### Ethical aspects and patient safety

The study has been approved by the Ethical Committees for the Capital Region of Denmark and reported to the Danish Data Protection Agency. All patients entering this study receive a higher level of diagnostics and treatment than standard care at the moment. The improved diagnostics and, thereby, the reduction of overtreatment will benefit the individual patient more than the disadvantage of delaying treatment. All data are kept under the same security as other sensitive data at a GP office. In case of any adverse event that could be attributed to participation in the trial (eg. worsening of symptoms due to delay of treatment), the GP in charge of care of the participant will follow a flow-chart to determine if the trial-responsible investigator should be notified and how fast. If the event is considered harmless or unlikely to be related to the trial, it is registered on the case-report form. If it is considered serious and likely related to the trial, the trial coordinator is contacted by telephone within 24 h. At least two members of the trial team evaluate serious events related to the trial and decide if the trial team should be gathered. All adverse events that could be attributed to participation in the trial are recorded and analyzed biannually by the coordination team. All results, positive, negative, and inconclusive, will be published.

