## Methods

### Study design

Randomized controlled open label trial of two diagnostic approaches in a primary care setting.

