## Discussion

In Denmark, POCT combined culture and susceptibility testing has been in use for decades, and the use has increased since introduction of the FLEXICULT™ SSI-Urinary Kit. Despite this popularity no clinical trials have yet validated its impact in clinical practice. This study will investigate the effect of POCT susceptibility testing on appropriate choice of antibiotics and on clinical and microbiological cure in patients with uncomplicated UTI in primary care in Denmark.

The clinical effect and cost-effectiveness of POCT culture and susceptibility testing in UTI is currently being investigated by another research group [15]. Although both studies aim at investigating the effect of the Flexicult on the appropriateness of antibiotic use and the impact on patient outcomes, there are at least three important differences. Firstly, in the study by Bates et al., the effect of combined culture and susceptibility testing is compared to various forms of standard care in a four-country multicenter setting. The focus of the present study is narrower, specifically aiming at determining the value of the susceptibility component compared to culture alone in a single region in Denmark. Secondly, all GPs in this study are experienced users of POCT susceptibility testing, and their skills are validated before enrollment of patients as described under the recruitment process, thus inter-practice variation is minimized. Thirdly, in this study, both groups will have treatment delayed until a positive culture is obtained, thereby minimizing the number of culture-negative patients receiving inappropriate antibiotic treatment.

We have chosen to include patients with diabetes, recurrent UTI and elderly patients when they are otherwise healthy and can be safely included. In the analysis, they are investigated for effect modification and, if the sample allows it, they are analyzed separately, since they could be expected to benefit more from the intervention than other groups.

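### A serious event that the unblinded treating GP judges unlikely to be related has no stated 24-hour notification or two-person evaluation, so recognition can wait for the twice-yearly analysis

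*Protocol article*

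**What the plan says.** The trial is described under Study design as "Randomized controlled open label trial of two diagnostic approaches in a primary care setting". The handling of adverse events is set out in one paragraph of the Protocol article, under Ethical aspects and patient safety. Its steps are:

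- **Entry:** "In case of any adverse event that could be attributed to participation in the trial".
- **Who classifies:** "the GP in charge of care of the participant will follow a flow-chart to determine if the trial-responsible investigator should be notified". The flow-chart itself is not reproduced in the article.
- **Form route:** "If the event is considered harmless or unlikely to be related to the trial, it is registered on the case-report form".
- **Rapid route:** "If it is considered serious and likely related to the trial, the trial coordinator is contacted by telephone within 24 h".
- **Second opinion:** "At least two members of the trial team evaluate serious events related to the trial".
- **Periodic analysis:** "All adverse events that could be attributed to participation in the trial are recorded and analyzed biannually by the coordination team".

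The Discussion adds that "both groups will have treatment delayed until a positive culture is obtained", so the wait for the plate is common to both arms.

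**The concern.** Relatedness is a weak gate for escalation in this trial, for three reasons.

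First, the risks that participation adds are a wait for the plate in both arms and, in the control arm, a drug chosen without a susceptibility result. Harm from either would look like progression of the urinary tract infection. A GP could reasonably put a hospital admission for ascending infection down to the disease.

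Second, the GP who gives the causality opinion also randomises the patient, records the randomisation group, reads the plate and decides on treatment (Patients; Case-report form). That GP knows the arm and is assessing the result of his or her own decision.

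Third, because both arms wait, a comparison of the arms cannot show harm from waiting. Prompt assessment of individual serious events is the main way to notice it.

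What is at stake is the speed and independence of that assessment. The same paragraph states that the benefit of better diagnostics outweighs the drawback of delayed treatment, and serious events after the delay are part of the evidence on that statement.

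**Working it through.** There is no plan figure to reproduce and no formula to apply. The check is to follow each kind of event through the printed sentences.

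| Event as the GP judges it | 24-hour call | Two-member evaluation | Twice-yearly analysis |
|---|---|---|---|
| (a) Serious, likely related | Yes | Yes | Yes |
| (b) Serious, attributable in principle but unlikely related | Not stated; form entry | Not stated | Yes, on the literal wording |
| (c) Serious, not attributable at all | Outside the entry condition | Not stated | Outside the wording |

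**Row (a).** The rapid-route sentence joins two conditions, seriousness and likely relatedness. Both are met.

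**Row (b), rapid route.** The form-route sentence joins its conditions with an *or*: an event goes to the form if it is harmless, or if it is unlikely to be related. The second condition does not mention seriousness, so a serious event satisfies it. The same event fails the likely-related half of the rapid-route condition. The two-member evaluation is stated for serious events that are related, and the only person so far to have judged relatedness is the GP, who has said it is unlikely.

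**Row (b), periodic analysis.** The entry sentence and the periodic sentence use the same criterion, that the event could be attributed to participation. Neither requires that attribution be likely. An event that met the criterion on entry and was then graded unlikely still meets it for the twice-yearly analysis.

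**Row (c).** An event the GP regards as not attributable at all never meets the entry criterion. The article does not say where the line between unlikely and not attributable lies, so the boundary between (b) and (c) rests with the GP.

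**Size of the delay in row (b).** Reading the interval as twice a year, the longest gap between analyses is 12 / 2 = 6 months, against 24 hours in row (a). Six months is the upper limit; an event just before a scheduled analysis would wait far less.

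**The case against.** Three arguments on the other side deserve weight.

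*The event is not lost.* A reader might infer that an event judged unlikely related goes to the form alone and escapes both rapid and periodic review. The documents do not support this. The article does not say that the form is the only destination, and the twice-yearly analysis has no filter on seriousness or on likelihood of relatedness. This argument stands in full and limits the point to delay and the missing second opinion. For the same reason, an estimate of events lost to review would have no basis; it would also need a complication rate and a misjudgement rate, neither of which is in the documents.

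*The flow-chart is not shown.* It decides whether and how fast the investigator is told, so it may hold more routes than the article prints. A reader might also infer that an event that is likely related and not harmless, but not serious, has no route at all. That cannot be claimed from a summary, and such an event is in any case within the twice-yearly analysis. This argument does not remove the main point, because the printed sentences do assign the unlikely-related event to the form, and the flow-chart should not contradict them.

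*There are other safeguards.* The paragraph names worsening of symptoms through delay as an example of an attributable event, which should steer GPs towards reporting it. Women with severe systemic symptoms, high fever, flank pain or compromised immunity are excluded. The diary records symptom severity, change of antibiotic and re-consultation on days 1–7, and there is a laboratory culture on day 14. No between-arm analysis of adverse events is described that could be distorted. These facts lower the expected number of serious events and provide some information that does not depend on the GP's opinion. They are not a substitute for prompt notice: the paper diary is sent in only from day 7, with a telephone reminder at day 10, and naming an example does not stop a GP from grading a particular case as unlikely.

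**Conclusion.** The point holds in a limited form. As printed, a serious event that the unblinded treating GP grades as unlikely to be related has no stated 24-hour notice and no stated evaluation by two team members. If it could be attributed to participation, it still enters the twice-yearly analysis, so the effect is delayed recognition, by at most about six months, and not exclusion.

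This rests on two assumptions: that the flow-chart follows the printed sentences, and that the review interval means twice a year. The number of events affected cannot be estimated from the documents. The primary and secondary outcomes and their analysis are not touched. It is a patient-safety improvement worth making because it is specific and cheap.

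**What to change.** Reword the safety paragraph and the flow-chart in three respects:

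1. The GP notifies the trial coordinator of every serious event within 24 hours, whatever the GP's view of relatedness. The GP's opinion is still recorded but no longer decides escalation.
2. The trial-team members already assigned to evaluate serious events judge causality for all of them.
3. The protocol states that all adverse events entered on the case-report form, including those marked unlikely to be related, are included in the twice-yearly analysis.

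The cost is a change of wording, a short notice to the participating practices, and a few extra telephone notifications for the existing team. No change to patient treatment, sample size or outcome analysis is involved.

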### Analysis

#### Sample size calculation

##### Primary outcome

The proportion of appropriately treated patients in the control group is assumed to be 70–80 % based on an assumption that POCT culture will be precise in determining UTI, but current local resistance rates in *E. Coli* (70–80 % of infections) of about 6–10 % to pivmecillinam (50 % of patients with UTI) and 30–40 % to sulfamethizole (30 % of patients with UTI) will result in inappropriate treatments as defined in Fig. 3 [3, 7]. To detect a statistically significant (*α* = 0.05) 10 percentage-point difference between the two groups with 80 % probability, assuming an intra-class correlation of 0.2 between patients in the same practice, a sample of 600 patients is needed. In order to take possible drop-outs and sub-analyses into account, the study aims to enroll 750 patients.

### Secondary outcomes

#### Clinical remission

McNulty and Ferry reported clinical cure rates of 69 % on day 5 after targeted treatment with trimethoprim and 44 % on day 5 empiric treatment with pivmecillinam respectively in patients with uncomplicated UTI [13, 14]. Assuming a cure rate of 60–70 % on the fourth day of treatment (day 5) in the intervention group, a difference of at least 15 percentage points could be detected with the chosen sample while accounting for a 25 % drop-out on clinical follow-up.

#### Bacteriological cure rate

Since bacteriological cure with empiric antibiotics on day 8–10 is about 90 % [14] as reported in a Swedish study, we are not expecting to see a significant difference between the groups regarding this outcome.

### Statistical analysis

Comparison of the two randomization groups for both the primary and the secondary outcomes will be done by means of an odds ratio (OR) from a logistic regression model; clustering within practices is adjusted for by generalized estimating equations (GEE). Analyses will be performed intention-to-treat, i.e., the patients are analyzed in the groups they are randomized to regardless of the treatment they actually received. Effect modification – whether the effect of the intervention differs between subgroups in the data – will be investigated for GP factors (organization of practice, performance in reading the POCT), patient factors (age, concurrent illness, socio-demographic data, initial symptom score) and microbiological factors (amount and species). If a sufficient sample is obtained, sub-group analysis will be performed for patients with diabetes, elderly patients and patients with recurrent UTI since these groups are expected to benefit the most from the intervention. In an additional analysis of the primary outcome, the group inappropriately treated will be divided into under-treated and over-treated and analyzed in multinomial logistic regression models. Comparison of cure-rates will be done with Kaplan-Meier curves and log-rank tests. A P-value of 0.05 will be considered significant. Analyses will be performed with SAS v9.4.

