#### Urine samples

A mid-stream urine sample from the day of consultation will be divided in two. One part is sent to the local microbiological department, and the other part will be examined at the general practice using the POCT. On day 14 another urine sample will be sent to the local microbiological laboratory for culture.

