#### Secondary outcomes

The proportion of patients who are asymptomatic on the fourth day of treatment (clinical cure) defined as the patient stating, her symptoms are completely gone regardless of symptom score. Data obtained from symptom diariesThe proportion of patients with no significant bacteriuria on day 14 (bacteriological cure). Data obtained from control urine sample

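### The cure outcomes are given two tests at 0.05, a practice-adjusted logistic OR and a log-rank test without practice, and the plan does not say which one decides

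*Protocol article*

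**What the plan says.** All of this is in the protocol article.

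- **First method (Statistical analysis).** The comparison of the arms "for both the primary and the secondary outcomes will be done by means of an odds ratio (OR) from a logistic regression model", and "clustering within practices is adjusted for by generalized estimating equations (GEE").
- **Second method (same paragraph, later).** "Comparison of cure-rates will be done with Kaplan-Meier curves and log-rank tests". The threshold follows shortly after: "A P-value of 0.05 will be considered significant".
- **Clinical cure (Secondary outcomes).** "The proportion of patients who are asymptomatic on the fourth day of treatment (clinical cure"), taken from the diary. The sample-size text for clinical remission places this on day 5 and states a detectable difference in percentage points.
- **Bacteriological cure (Secondary outcomes; Urine samples).** A proportion on day 14. There is one follow-up specimen: "On day 14 another urine sample will be sent to the local microbiological laboratory for culture".
- **Diary (Symptom diary).** A daily item asks whether symptoms are completely gone, and the day of becoming symptom-free is recorded, over days 1–7.

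**The concern.** The two secondary outcomes are the two cure outcomes, so the second method falls on outcomes that already have a test. No order is given. The same paragraph labels the multinomial model as additional but gives the log-rank no such label.

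Three things follow.

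1. Clinical cure could be reported from whichever test is favourable. This matters because clinical benefit is the second of the two research questions in the Background, and cure is self-reported in an open-label trial.
2. The log-rank answers a different question from the outcome as defined. Curves can separate early and meet by day 5, and symptoms can return after a first symptom-free day.
3. The practice adjustment is attached to the logistic model. The log-rank as written has none.

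**Working it through.** **1. What the plan was sized for.** Inputs from the sample-size text on clinical remission: 60–70% cured in the intervention arm, a 15-point difference, 25% drop-out. Per arm this leaves 600 × 0.75 / 2 = 225, or 750 × 0.75 / 2 = 281.25.

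Power = Φ{[d√n − 1.96√(2p̄(1−p̄))] / √(p₁(1−p₁) + p₂(1−p₂))}.

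For 65% v 50%, p̄ = 0.575, so the two roots are √0.48875 = 0.699 and √0.4775 = 0.691.

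- n = 225: (2.250 − 1.370) / 0.691 = 1.27, power 90%.
- n = 281.25: (2.516 − 1.370) / 0.691 = 1.66, power 95%.

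Over the whole 60–70% range the power is 89–91% at 600 and 95–96% at 750, ignoring clustering. The 15-point statement is therefore attainable for a comparison of proportions. Nothing was sized for a log-rank test.

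**2. Which outcomes have an event time.**

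| Outcome | Defined as | Observed | Event time |
|---|---|---|---|
| Clinical cure | proportion, day 5 | daily, days 1–7 | yes |
| Bacteriological cure | proportion, day 14 | once after baseline | no |

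The survival sentence names neither outcome. The article uses the term for both: a sample-size subsection is headed "Bacteriological cure rate", and the Abstract and Background also speak of microbiological cure rates.

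**3. Two eligible tests for clinical cure.** The ceiling for two independent tests is 1 − 0.95² = 9.75%. The real tests are correlated, so this was simulated under the null: 3,000 trials, 50 practices of 15, blocks of 10 within practice, 25% of diaries missing, and a constant daily chance of cure giving about 63–65% symptom-free by day 5. The blocks within practice, the constant hazard and the practice SD are assumptions. Rejection at 0.05:

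| | No practice effect | Practice SD 1.0 (logit hazard) |
|---|---|---|
| GEE logistic OR, day 5 | 5.2% | 6.2% |
| Plain log-rank | 5.3% | 3.3% |
| Log-rank stratified by practice | 5.0% | 4.9% |
| Either GEE or plain log-rank | 7.8% | 7.1% |

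The simulation standard error near 7% is √(0.07 × 0.93 / 3000) = 0.5 points. A separate run of 4,000 null trials with 281 per arm, no practice effect and a plain test of proportions gave 4.4% and 4.9% singly and 6.7% for either. Taken together: about 6–8%.

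The log-rank's own contribution over the GEE test is 7.8 − 5.2 = 2.6 points without a practice effect and 7.1 − 6.2 = 0.9 points with one. In the second case part of the excess belongs to the GEE test itself.

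**4. Leaving practice out.** When practices differ and each contributes patients to both arms, between-practice variation cancels from the difference between arms but stays in the plain log-rank's variance. The test is then conservative: about 3% in place of 5%. Under a simulated treatment effect at practice SD 1.0, power was 67% for the plain log-rank and 78% for the stratified one. That pair depends on the effect put in, which is not a figure from the article, so it shows direction and rough size only.

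**The case against.** The best defence is that the natural reading is harmless. The outcomes are defined as proportions, the paragraph opens by giving them to the odds ratio, and clinical cure is sized as a difference in proportions. The log-rank comes after effect modification, subgroups and the multinomial model, and the diary collects exactly what a Kaplan-Meier curve of time to symptom-free needs. A condensed article may also leave the rank and stratification of a supportive test to a fuller document.

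Much of this stands. Kaplan-Meier for time to symptom-free is legitimate, and the lack of stratification alone would be a detail. What remains is a positive statement: two methods for comparing cure under one significance threshold, with no label on the second.

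Some stronger readings do not hold:

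- A reader might infer that the plan will draw survival curves for the day-14 culture. The article never says so; the sentence may be meant for clinical cure only. The fault is ambiguity.
- A reader might infer that the log-rank is the only comparison left without practice adjustment. The multinomial model is also described without it.
- A reader might apply the ICC of 0.2, or the power for 70% v 80%, to cure. Both belong to the primary outcome; the article gives no ICC for cure.
- A reader might infer that ignoring practice produces false positives. Under individual randomisation balanced within practice it does the opposite. The article states blocks of 10 but not that they are within practice.

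**Conclusion.** The point holds as a moderate one, confined to secondary outcomes. The primary outcome has one clearly assigned main test and is untouched.

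The main fault is the unordered pair of tests on clinical cure, which address different quantities. Its cost is a null chance of about 6–8% in place of 5% if either may be called the result. The second is the log-rank without practice, which costs power and does not inflate error. That conclusion rests on two assumptions the article does not state for cure: that cure varies by practice, and that allocation is balanced within practice. The third is wording that does not exclude the day-14 culture, for which no event time exists.

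**What to change.** In the Statistical analysis section:

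1. State that the GEE logistic odds ratio is the single test of each cure proportion: clinical cure on the fourth day of treatment (day 5) and bacteriological cure on day 14.
2. Replace the survival sentence by one saying that time to becoming symptom-free, from the diary over days 1–7, will be shown by Kaplan-Meier curves and compared by a log-rank test stratified by practice, as a supportive analysis, and that the day-14 culture is not part of it.

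The cost is two sentences. No data collection, sample size or patient burden changes. If practices do not in fact differ, stratifying loses a little power in a test that is only supportive.

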## Discussion

In Denmark, POCT combined culture and susceptibility testing has been in use for decades, and the use has increased since introduction of the FLEXICULT™ SSI-Urinary Kit. Despite this popularity no clinical trials have yet validated its impact in clinical practice. This study will investigate the effect of POCT susceptibility testing on appropriate choice of antibiotics and on clinical and microbiological cure in patients with uncomplicated UTI in primary care in Denmark.

The clinical effect and cost-effectiveness of POCT culture and susceptibility testing in UTI is currently being investigated by another research group [15]. Although both studies aim at investigating the effect of the Flexicult on the appropriateness of antibiotic use and the impact on patient outcomes, there are at least three important differences. Firstly, in the study by Bates et al., the effect of combined culture and susceptibility testing is compared to various forms of standard care in a four-country multicenter setting. The focus of the present study is narrower, specifically aiming at determining the value of the susceptibility component compared to culture alone in a single region in Denmark. Secondly, all GPs in this study are experienced users of POCT susceptibility testing, and their skills are validated before enrollment of patients as described under the recruitment process, thus inter-practice variation is minimized. Thirdly, in this study, both groups will have treatment delayed until a positive culture is obtained, thereby minimizing the number of culture-negative patients receiving inappropriate antibiotic treatment.

We have chosen to include patients with diabetes, recurrent UTI and elderly patients when they are otherwise healthy and can be safely included. In the analysis, they are investigated for effect modification and, if the sample allows it, they are analyzed separately, since they could be expected to benefit more from the intervention than other groups.

A challenge of this study is the similarity between the intervention and control groups. The potential difference between the groups in this study will mainly be driven by those patients in the control group receiving an antibiotic to which, the infecting pathogen is resistant. Since *in vitro* resistance rates in Denmark against the most commonly used antibiotics for UTI are 15–40 %, the effect could turn out minor at present [3]. If the study detects no additional benefit of susceptibility testing over culture alone, this will provide important information for the Danish national health care system. However, the results may not be directly applicable to countries outside Scandinavia. On the other hand, if susceptibility testing proves superior to culture alone, the impact of such a finding will likely be much higher in countries where resistance rates are higher. In conclusion, the present study will test the hypothesis that POCT susceptibility testing for uncomplicated UTI and individually targeted therapy will decrease the use of inappropriate antibiotics and positively influence clinical cure rates. If this proves true, the results of the study may provide important evidence to recommend POCT susceptibility testing for patients with suspected UTI. This could become one of many strategies to fight antibiotic resistance.

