**Discussion:**

The results of this study may provide important evidence to recommend POCT culture and susceptibility testing in all patients with suspected uncomplicated UTI. This could become an additional strategy to fight antibiotic resistance.

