#### Microbiological analyses performed on-site at the general practice

##### Culture (control group)

Point-of-care culture will be performed using ID Flexicult™ (SSI DIagnostica, Denmark) which is a chromogenic agar plate for identification and quantitation of urinary tract pathogens. The sample is seeded with a 10 μL inoculation needle, the lid is applied, and the agar plate incubated upside down at 35 °C overnight. The plate is read the next day. If it is positive, no further incubation is needed, if it is negative, incubation is continued until 24 h after inoculation. The bacterial identification is based on colony color and size. The agar plate can be seen on the right side of Fig. 2.

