##### Culture and susceptibility testing (intervention group)

Urine culture and susceptibility testing will be performed on the intervention group by means of a POCT, the FLEXICULT™ SSI-Urinary Kit (SSI Diagnostica, Denmark). The kit is a chromogen agar in an ordinary Petri dish, but with higher sides. The Petri dish is divided into 6 compartments: 1 large compartment for quantitative analysis and 5 smaller compartments for susceptibility testing. The agar in each of the smaller compartments contains 1 of 5 antimicrobials: trimethoprim, sulfamethoxazole, ampicillin, nitrofurantoin, and mecillinam. The agar plate can be seen on the left side of Fig. 2.

The agar plate is flooded with the urine specimen for a couple of seconds and then incubated at 35 °C over night. The plate is read on the following day.

As the concentrations of the antimicrobials in the 5 smaller compartments are adjusted in accordance with breakpoints, growth on these compartments indicates resistance of the pathogen in question and hence a potential risk of treatment failure.

Figure 1 illustrates the data collection process and Fig. 2 explains the study design and the difference between the intervention and control arm.

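### The arms differ in culture plate and inoculation as well as in susceptibility testing, so the primary odds ratio compares two test packages and cannot be credited to the susceptibility component alone

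*Protocol article*

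**What the plan says.** The Discussion sets the trial apart from a similar study by its narrower aim, "specifically aiming at determining the value of the susceptibility component compared to culture alone". Its closing paragraph expects any difference to come mainly from controls who are given a drug to which the pathogen is resistant.

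The two culture sections describe different tests. For controls, "Point-of-care culture will be performed using ID Flexicult"; "The sample is seeded with a 10 μL inoculation needle, the lid is applied"; and for the reading, "if it is negative, incubation is continued until 24 h after inoculation". The intervention arm uses the FLEXICULT SSI-Urinary Kit, with one large compartment for quantitative culture and five that contain antimicrobials: "The agar plate is flooded with the urine specimen for a couple of seconds", followed by overnight incubation and reading the next day.

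Under Primary outcome, treatment is judged against the laboratory culture. A woman with significant growth must receive a suitable antibiotic; a woman without it must receive none. Sample size calculation assumes that point-of-care culture identifies infection precisely and makes no separate assumption for each plate.

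The Abstract's Discussion says that the results may support a move to "recommend POCT culture and susceptibility testing in all patients with suspected uncomplicated UTI".

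**The concern.** To isolate susceptibility testing, the arms would have to share the same culture and differ only in the added susceptibility result. Here plate format and inoculation method change with it. Randomization cannot separate these effects, because the plate is part of the assigned arm.

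This matters because the primary outcome is not about drug choice alone. A false-positive plate can lead to an antibiotic where the laboratory finds no growth. A false-negative plate can leave an infection untreated. Both count as inappropriate. If the plates differ in either error rate, the difference enters the primary odds ratio and would be reported as the value of susceptibility testing. In the opposite direction it would hide a real benefit.

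**Working it through.** 1. **What differs by arm** (the two culture sections). Plate: ID Flexicult against the compartmented kit. Inoculation: 10 μL needle against flooding. Negative plates: continued to 24 h in the control text, with no such statement in the intervention text. The exclusion criteria speak of reading after 24 h for everyone, so the last item may be a difference in description only. The first two are real.

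2. **How the plate reaches the outcome** (Primary outcome). Let π be the proportion with significant growth in the day-0 laboratory culture, Se and Sp the plate's sensitivity and specificity, and d the probability that a treated, infected woman receives an appropriate drug. If treatment follows the plate:

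   P(appropriate) = π × Se × d + (1 − π) × Sp

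   Susceptibility testing is meant to act through d. The plate acts through Se and Sp. With d equal in both arms, the plates alone give a difference of π × d × ΔSe + (1 − π) × ΔSp.

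3. **The plan's own figure.** For 70% against 80%, two-sided 5%, power 80%: n per arm = [1.96 × √(2 × 0.75 × 0.25) + 0.8416 × √(0.7 × 0.3 + 0.8 × 0.2)]² / 0.10² = 294 after rounding up, or 588 in total, close to the stated 600. This match uses no clustering term, and nothing below depends on it. The 10-point target is the yardstick.

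4. **Illustrative plate shifts.** The documents give no plate accuracy, so these inputs are assumptions: π = 50–80%, d = 75–85%, gaps of 5 or 10 points.
   - Specificity gap of 5 points: 0.20 × 5 = 1.0; 0.35 × 5 = 1.75; 0.50 × 5 = 2.5. For a 10-point gap: 2.0 to 5.0.
   - Sensitivity gap of 5 points: 0.50 × 0.75 × 5 = 1.9, up to 0.80 × 0.85 × 5 = 3.4.
   - Both gaps of 5 points favouring the same plate: 0.80 × 0.75 × 5 + 0.20 × 5 = 4.0, up to 0.50 × 0.85 × 5 + 0.50 × 5 = 4.6.
   - Gaps of 5 points in opposite directions: from 0.50 × 0.75 × 5 − 0.50 × 5 = −0.6 to 0.80 × 0.85 × 5 − 0.20 × 5 = +2.4.

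5. **Effect on the test.** Suppose susceptibility testing does nothing, there are 300 women per arm, the control rate is 70–80%, and a simple two-sided 5% comparison of proportions is used. The probability of a significant result in the better plate's favour is about 8–9% for a 2-point shift, 13–16% for 3 points and 28–36% for 5 points. With no shift it is 2.5%.

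6. **Where the two effects can be told apart.** Among laboratory-positive women, P(appropriate) = Se × d. A 5-point sensitivity gap still moves this by 0.75 × 5 = 3.75 to 0.85 × 5 = 4.25 points, so this stratum as a whole does not isolate susceptibility testing. Wrong-drug errors among all randomized women are π × Se × (1 − d). The same gap moves these by only 0.50 × 0.15 × 5 = 0.4 to 0.80 × 0.25 × 5 = 1.0 points. A less sensitive plate would lower them, because fewer infected women are treated at all.

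**The case against.** The strongest reply is that Study design announces a randomized comparison of two diagnostic approaches, and that comparison is estimated without bias whatever the plates do. This stands. A reader might infer that the primary result is invalid, or that none of it can be credited to susceptibility testing; the documents support neither. The closing paragraph of the Discussion also says only that the difference will mainly come from resistant pathogens.

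The plan does more than assume accuracy. GPs are trained and tested on reading the plate, the day-0 laboratory sample is a quality control of the practice result, and reading performance is examined as an effect modifier. These safeguards are useful, but none is stated as a way to separate plate from susceptibility effect.

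The planned split into under- and over-treatment probably already captures false-positive plates, since an antibiotic without laboratory growth can occur only in laboratory-negative women. The exact categories are in a figure that is not shown. The remaining gap is narrower: under-treatment may mix missed infections with wrong drugs.

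Finally, both plates are chromogenic, come from the same manufacturer and are incubated at 35 °C. They may perform alike, and opposite gaps would partly cancel. That is a fair reason not to presume a large effect, but it does not show equivalence.

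**Conclusion.** The point holds as one of attribution. Plate and inoculation differ by arm, the treat/no-treat decision is part of the primary outcome, and nothing in the article shows the plates to be equally accurate. The primary odds ratio therefore answers a question about two test packages, not the narrower one that the Discussion claims to isolate.

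The size is unknown. The 1.0–2.5 points for a 5-point specificity gap, and the larger figures when sensitivity gaps are added, rest on assumed prevalence, drug-choice probability and accuracy gaps, and on treatment following the plate. They show that a plate effect could be a noticeable share of a 10-point target. They are no evidence that one exists, or of which arm it would favour.

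Two further inferences should be resisted. One is that the laboratory-positive result as a whole measures susceptibility testing; step 6 shows that it does not. The other is that the Abstract's forward-looking sentence is an error in the plan. It is hedged. It does, however, reach further than the design: dip-stick-negative women are excluded and both arms receive culture with treatment delayed until the plate is read. The conclusion should stay within those limits.

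**What to change.** 1. Pre-specify each plate's sensitivity and specificity against the day-0 laboratory result, reported by arm.
2. Extend the planned under-/over-treatment model. By day-0 laboratory status, split inappropriate treatment into antibiotic given without growth, infection left untreated, and wrong drug given. Keep all randomized women in the denominator; restricting to treated women would select on something that happens after randomization. Take only an arm difference in wrong-drug errors as evidence for the susceptibility component, and read it beside the difference in missed infections. Do not credit the whole laboratory-positive result to susceptibility testing.
3. Word the conclusion as the effect of this culture-plus-susceptibility kit against this culture-only plate, in dip-stick-positive women whose treatment waits for the plate reading.

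The cost is a few extra tables from data already collected and a narrower claim. Design, sample size and primary analysis stay as they are.
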